### Sample size

In a previous RCT, the i-Sleep intervention demonstrated an effect size of 1.06 on Sleep Quality (Pittsburgh Sleep Quality Inventory, [42]). However, a recent meta-analysis [40] on self-help for insomnia demonstrates somewhat more modest effect sizes; a Hedges’ *g* of 0.80, 0.66 and 0.55 respectively for sleep efficiency, sleep onset latency and wake after sleep onset at immediate post treatment. For the current study we will use a conservative estimation of a post treatment effect size, a Cohen’s *d* of 0.50, on the primary outcome insomnia severity. Using a power of 80 %, an alpha of 0.05, and a study dropout rate of 20 %, we need to include 80 patients in both conditions, 160 in total, to answer our primary research question.

### Statistical analysis

The study will be conducted in adherence to the Consolidated Standards of Reporting Trials (CONSORT; [65]) statement. For all analyses statistical significance will be set at *p* < .05. In accordance with the intention-to-treat principle, we will use all data independent of treatment or study completion. Missing values will be imputed using multiple imputation for calculation of Cohen’s *d* [66, 67].

Between group interaction effects (time × group) will be tested with Generalized Estimating Equations (GEE). Variables that are not distributed equally or that predict dropout will be added to the model as covariates. This technique is suitable for the analysis of the longitudinal relationship between a continuous outcome variable and several time-dependent and time independent covariates [68].

We will describe the magnitude of the effect (effect size) with Cohen’s *d*. We will calculate this by dividing the difference in scores of the two groups at post-test by the pooled standard deviation of change scores (Cohen’s *d*). This can thus be interpreted as the number of standard deviations the intervention group scores better than the control group [69].

Next, we will compare the intervention and control group with regard to the percentage of patients who have (1) improved and (2) recovered. An ISI score of 10 or lower will be considered recovery. Improvement will be defined as an ISI change score of 7 points or more [50]. This information will be used to calculate the relative risk and the number needed to treat [70].

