### Assessments

Four assessments will take place: at baseline (T0), 8 weeks post-treatment (T1), 6- (T2) and 12-month (T3) follow-up. For an overview of the measurements see Table 2. Questionnaires will be administered online. Additionally, participants will receive an actigraphic watch and a sleep diary by mail at all assessments. Patients are asked to wear the actigraphic watch for 7 days while also filling out the sleep diary for these same days [48]. Additionally, data extracted from the electronic medical records in general practice will be used to assess consumption of care and prescription of sleep medication, up to 12 months follow-up.

**Table 2 Tab2:** Measurements and instruments at different point of assessment

Measurement	Instrument	Baseline (T0)	T1, T2 and T3 (at 8, 26 and 52 weeks)
Background characteristics	n/a	X	-
History of insomnia	n/a	X	
Alcohol use	AUDIT	X	X
Insomnia severity	ISI	X	X
Anxiety and depression	HADS	X	X
Daytime insomnia consequences	Espie et al., 2012	X	X
Daytime functioning	WSAS	X	X
Fatigue	FSS	X	X
Quality of life	EQ-5D-5 L	X	X
Healthcare utilization & work absenteeism	TiC-P	X	X
Treatment satisfaction	n/a	-	T1
Actigraphy	Actigraph GT9X Link	X	X
Sleep diary	Consensus diary	X	X
Sleep medication	n/a	X	X

AUDIT: Alcohol Use Disorders Identification Test; ISI: Insomnia Severity Index; HADS: Hamilton Anxiety and Depression Scale; WSAS: Work and Social Adjustment scale; FSS: Fatigue Severity Scale; EQ-5D-L: EuroQoL; TiC-P: Trimbos and iMTA questionnaire on Costs associated with Psychiatric Illness

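### The sample size is set for a post-treatment ISI difference, but the planned time × group GEE test names no contrast, so the stated 80% power is not tied to it

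*Protocol article*

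**What the plan says.** The protocol article, Sample size, bases the trial on "a conservative estimation of a post treatment effect size, a Cohen’s *d* of 0.50, on the primary outcome insomnia severity". The remaining inputs follow: "Using a power of 80 %, an alpha of 0.05, and a study dropout rate of 20" %. The conclusion is that "we need to include 80 patients in both conditions, 160 in total, to answer our primary research question". This section mentions no repeated measures, correlation between assessments or interaction.

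The Statistical analysis section gives the test: "Between group interaction effects (time × group) will be tested with Generalized Estimating Equations (GEE"). It adds, under intention to treat, that "we will use all data independent of treatment or study completion". The effect size is to be obtained by "dividing the difference in scores of the two groups at post-test by the pooled standard deviation of change scores".

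On timing, the Assessments section says: "Four assessments will take place: at baseline (T0), 8 weeks post-treatment (T1), 6- (T2) and 12-month (T3) follow-up". The Primary outcome section names the ISI without an assessment time. The Study design section says that controls are offered i-Sleep six months after inclusion, which is before T3.

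**The concern.** A sample size is justified for one contrast. Here that contrast is a group difference after treatment, whereas the stated test is a time × group interaction. With four assessments, that phrase can mean a change from T0 to T1, a joint test over several follow-ups, or a difference in linear slope. These answer different questions and have different power. The article does not say which one decides the trial.

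Two things are at stake. First, the 80% power can be credited to the primary test only once that test is identified. Second, if the term chosen includes T3, the result partly reflects what happens after controls are offered the intervention. A benefit at T1 and T2 could then be diluted or, with a linear slope, reversed in sign.

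**Working it through.** **Inputs from the article.** d = 0.50 on the ISI post-treatment, power 80%, alpha 0.05, dropout 20% (Sample size); 1:1 allocation (Randomization); assessments at 0, 8, 26 and 52 weeks (Assessments, Table 2).

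**Assumptions, not in the article.** Two-sided test; equal variances; the same correlation r between any two assessments, shown at 0.3, 0.5 and 0.7; 64 completers per arm. Unless stated otherwise, d is in units of the post-score SD. Positive effects favour i-Sleep.

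**Step 1: the stated figure.** For a two-sided two-sample t-test with d = 0.50, 63 per arm give 79.5% power and 64 give 80.1%. Then 64 / 0.8 = 80 per arm, 160 in total. The figure reproduces exactly as a comparison at one time point.

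**Step 2: T0-T1 interaction.** This compares change scores between two groups. The SD of change is √(2(1 − r)) post-score SDs, so the standardised effect is 0.50 / √(2(1 − r)).

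- r = 0.3: 0.423, power 66%
- r = 0.5: 0.500, power 80%
- r = 0.7: 0.645, power 95%

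If the planning d of 0.50 is instead in units of the SD of change, as in the article's own definition of Cohen's d, the standardised effect is 0.50 at every r and power is 80.1% throughout.

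**Step 3: readings that use all four assessments.** The joint 3-df test has noncentrality [32 / (1 − r)] × [Σδ² − (Σδ)² / 4], where δ are the effects at T1 to T3 and 32 = 64 / 2. For a constant 0.50 at r = 0.5 this is 64 × (0.75 − 0.5625) = 12, which gives 84%.

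For a slope linear in weeks, the deviations from the mean of 21.5 weeks are −21.5, −13.5, 4.5 and 30.5, with sum of squares 1,595. The standard error is √[(2 / 64)(1 − r) / 1,595].

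| Effect at T1, T2, T3 | Joint 3-df test (r = 0.3 / 0.5 / 0.7) | Linear slope (r = 0.3 / 0.5 / 0.7) |
|---|---|---|
| 0.50, 0.50, 0.50 | 69% / 84% / 98% | 44% / 58% / 79% |
| 0.50, 0.35, 0.20 | 54% / 70% / 91% | 5% / 5% / 6% |
| 0.50, 0.50, 0 | 82% / 93% / >99% | 12% / 15% / 21% |

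The last row represents controls catching up fully by T3. The expected slope is then 0.50 × (−13.5 + 4.5) / 1,595 = −0.0028 per week, which points against i-Sleep. The joint test rejects often, but partly because the groups converge.

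**Step 4: baseline-adjusted T1 contrast.** The standardised effect is 0.50 / √(1 − r²).

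- r = 0.3: 0.524, power 84%
- r = 0.5: 0.577, power 90%
- r = 0.7: 0.700, power 98%

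At r = 0 it equals the t-test of Step 1, so power does not fall below the stated 80%. If d is on the SD-of-change scale, the effect is 0.50 × √(2 / (1 + r)) = 0.620, 0.577 and 0.542, with power 94%, 90% and 86%.

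**The case against.** The strongest reply is that the two sections are compatible. Under randomisation the expected baseline difference is zero, so the T0-T1 interaction estimates the same quantity as the post-treatment difference; only its variance differs. With d on the change-score scale that the article itself uses, 160 patients give 80% power for that term. Both the sample size and the effect-size definition point to T1. The choice of model term, time coding and baseline handling is often left to a full protocol or analysis plan, and neither is shown.

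Much of this stands. A reader might infer that the interaction is tested over all four assessments, that the 80% therefore cannot apply, and that the trial is underpowered. The article supports none of these steps. It does not say which assessments enter the test. The sentence on using all data is about intention to treat and does not define a joint test. The low figures above need an assumed low correlation, a fading effect or a linear slope, and the article states none of them.

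What does not stand is that the match can be taken for granted. It requires the tested term to be T0-T1, which is stated nowhere, and either r of about 0.5 or more or a change-score d. The Sample size section does not give the SD scale of its d. The article itself prints both the justification of N and the test, and does not link them.

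**Conclusion.** The point holds as a missing link between sample size and test, not as a demonstrated power error. The 160 patients are exactly right for a two-group comparison at one time point. The stated 80% carries over to a T0-T1 interaction if the pre-post correlation is at least about 0.5, or at any correlation if d is on the change-score scale. For readings that use all four assessments, power runs from about 5% to over 99%. That range comes from the assumed correlation, time coding and course of effect, so it shows dependence on an unstated choice and no definite shortfall.

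Two conclusions are firmer. An interaction that includes T3 does not compare i-Sleep with care-as-usual alone, because controls are offered i-Sleep at six months. And with d on the post-score scale, a baseline-adjusted T1 contrast uses data already planned and has 84% to 98% power, against 66% to 95% for the T0-T1 interaction, at correlations of 0.3 to 0.7.

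**What to change.** In Statistical analysis:

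- Name the i-Sleep minus care-as-usual difference in ISI at T1 (8 weeks) as the primary contrast, two-sided alpha 0.05.
- Estimate it from the GEE with time as a categorical variable and baseline ISI as a covariate, or with baseline means constrained equal across arms.
- State that the primary claim does not rest on an interaction that includes T3.

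In Sample size, say whether the planning d of 0.50 is in units of the post-score SD or the SD of change.

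If the investigators prefer a joint test, they should instead justify N for it with an assumed correlation and course of effect. Naming the T2 difference as key secondary is optional.

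The cost is one paragraph of wording, with no extra patients, visits or data. The article reports that the first participants are being recruited, so the change can be made before outcome data are seen.

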### Randomization

After inclusion patients are randomized by an independent researcher using random sequence block randomization (blocks of 2, 4 or 6), stratified by whether or not they have used sleep medication in the past 4 weeks and by individual PWP, on a 1:1 ratio. After inclusion of a patient the independent researcher reveals the next randomization outcome. Due to the nature of the study, blinding of the researchers, PWPs or patients is not possible.

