### Primary outcome: insomnia severity

The primary outcome of the study will be insomnia severity as measured by the Insomnia Severity Index [49]. The ISI consists of 7 items scored on a 5-point Likert scale (0 = not at all, 4 = extremely) and scores range from 0–28, higher scores indicating more severe insomnia. The ISI assesses the nature, severity and the impact of insomnia. Previous research has indicated that the Insomnia Severity Index (ISI) is a valid and reliable instrument to quantify perceived insomnia severity and presents a clinically useful tool in screening as well as outcome measurement. It possesses adequate internal consistency (Cronbach’s alpha = .90), is sensitive to changes in perceived sleep difficulties over time [50] and has been validated for online use [51]. We use a community sample cut-off score of ≥10 to define clinical insomnia [50].

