### Cost-effectiveness and cost-utility analysis

Both cost-effectiveness and cost-utility analyses will be performed. Cost-effectiveness analysis entails measuring the value of the new therapy i-Sleep by calculating the difference in costs between i-Sleep and care-as-usual, and dividing this by the difference in effectiveness of both treatment options (i.e., calculating the cost-effectiveness ratio) [71, 72].

The cost-utility analysis represents the costs associated with gaining one quality-adjusted life year (QALY). Missing cost and effect data will be imputed using multiple imputation. Seemingly unrelated regression will be used to estimate cost and effect differences while adjusting for potential confounders. We will use bootstrapping to estimate uncertainty surrounding the cost-effectiveness estimates to account for the skewed distribution of costs. Cost-effectiveness planes and cost-effectiveness acceptability curves will be estimated to show statistical uncertainty surrounding the cost-effectiveness estimates.

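### The primary GEE takes its covariates from observed imbalance or dropout, so neither baseline ISI nor the stratification factors are assured a place in the model

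*Protocol article*

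**What the plan says.** Under Primary outcome, the Protocol article names the endpoint: "The primary outcome of the study will be insomnia severity as measured by the Insomnia Severity Index". It is measured at every visit: "Four assessments will take place: at baseline (T0), 8 weeks post-treatment (T1), 6- (T2) and 12-month (T3) follow-up". The Statistical analysis section gives the model: "Between group interaction effects (time × group) will be tested with Generalized Estimating Equations (GEE"). It then gives the rule for covariates: "Variables that are not distributed equally or that predict dropout will be added to the model as covariates". It lists no candidate variables, no test or cut-off for imbalance, no criterion for predicting dropout, and no covariate that is always included.

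The Randomization section says that allocation is "stratified by whether or not they have used sleep medication in the past 4 weeks and by individual PWP, on a 1:1 ratio", and that researchers, PWPs and patients cannot be blinded. The analysis section does not carry the two stratification factors into the model.

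The Sample size section assumes "a Cohen’s *d* of 0.50, on the primary outcome insomnia severity" after treatment, 80% power, alpha 0.05 and 20% dropout, giving 80 per arm.

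**The concern.** This is a stated rule, not detail left to a fuller document, and the rule is poorly chosen for three reasons.

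- **Wrong criterion.** In a randomised trial, baseline differences between arms are chance. A covariate earns its place by predicting ISI, and observed imbalance does not measure that.
- **Model settled late.** Imbalance can be judged only with allocation known, and dropout prediction only once follow-up is in. With unblinded researchers and no threshold, several models would all comply with the text.
- **Important variables left to luck.** Stratified randomisation tends to balance sleep medication and PWP, so an imbalance rule will seldom select them. Baseline ISI, the obvious prognostic variable, enters as a covariate only if it happens to differ between arms or predict dropout.

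At stake are the precision of the primary estimate and the reader's confidence that the model was not chosen for its result.

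**Working it through.** **1. The plan's own figure.** With d = 0.50, two-sided alpha 0.05 (sidedness is not stated; one-sided does not reproduce) and 80% power, the normal formula gives 2 × (1.960 + 0.842)² / 0.50² = 62.8, so 63 per arm. The exact t-test gives 64. Then 64 / (1 − 0.20) = 80 per arm, 160 in total. The stated figure reproduces and uses no covariate gain.

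**2. What baseline adjustment would add.** Inputs: 64 completers per arm and d = 0.50 from the Sample size section. Assumptions: d is on the scale of the post-treatment SD, the SD is equal at baseline and follow-up, and the baseline-to-post correlation r is 0.3 to 0.7 (the article gives none).

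Power ≈ Φ(d × √(n/2) / k − 1.960), with d × √(n/2) = 0.50 × √32 = 2.828 and
- post-only comparison: k = 1
- change-type contrast (T0 as an outcome): k = √(2(1 − r))
- baseline as covariate: k = √(1 − r²)

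| r | Post-only | Change-type | Baseline-adjusted |
|---|---|---|---|
| 0.3 | 0.807 | 0.667 | 0.843 |
| 0.5 | 0.807 | 0.807 | 0.904 |
| 0.7 | 0.807 | 0.955 | 0.977 |

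Example at r = 0.5, adjusted: 2.828 / √0.75 = 3.266; 3.266 − 1.960 = 1.306; Φ = 0.904. The exact t-test value for post-only is 0.801. The variance ratio of adjusted to change-type is (1 + r)/2, which is 0.65, 0.75 and 0.85.

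**3. What the rule recovers if T0 is not an outcome.** Simulation used 6,000 trials per scenario, 64 per arm, d = 0.50, baseline ISI as the only candidate, and imbalance taken as p<0.05 (an assumed threshold):

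| r | Unadjusted | Rule | Named in advance |
|---|---|---|---|
| 0.3 | 80% | 81% | 84% |
| 0.5 | 79% | 80% | 89% |
| 0.7 | 80% | 82% | 98% |

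With eight independent candidates of joint R² = 0.30 (assumed), the rule selected at least one in about 34% of trials. Power was 81% under the rule, 80% unadjusted and 90% with all eight fixed. At R² = 0.20 it was 80%, 80% and 86%.

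**4. What the rule does if T0 is an outcome.** This is the more natural reading of a time × group test. A time-constant covariate entered as a main effect then cancels from the within-person contrast. In an exchangeable GEE with complete data, the interaction estimate and its standard error were the same with and without such a covariate. With roughly 20% covariate-dependent dropout, the mean absolute shift was 0.02 SD, and power was 86% against 87%. On this reading the rule does not correct the imbalance it targets.

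**5. Type I error (post-only model).** Fixed at p<0.05, the rule gave 3.6% to 4.6%. Taking the best result among no adjustment and cut-offs of 0.05, 0.10 and 0.20, with eight candidates, gave 6.1% to 6.4%.

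**The case against.** The strongest defence is that the planned model is a longitudinal GEE. If T0 is an outcome, baseline ISI is already used, and choosing other baseline covariates hardly moves the primary contrast (step 4). That stands, and it limits both the discretion and the gain from additional main-effect covariates. It does not save the rule, which then fails at its own purpose and leaves a change-type contrast less efficient than baseline adjustment at every correlation shown.

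Dropout predictors also have a legitimate role. Multiple imputation is described for Cohen's d, and the article does not say that the GEE runs on imputed data. Conditioning on predictors of missingness can therefore protect the primary test. This stands: these variables should be kept, but named in advance.

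A reader might also infer more than the documents support:

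- **Inflated type I error.** A mechanical p<0.05 rule is slightly conservative. The 6.1% to 6.4% requires picking the best of several cut-offs, which the article does not propose, although the undefined criterion does not prevent it.
- **An underpowered trial.** The 160 does not rely on covariates.
- **The same fault in the QALY analysis.** The Cost-effectiveness section says only that "Seemingly unrelated regression will be used to estimate cost and effect differences while adjusting for potential confounders". It states no data-driven selection rule and no condition on baseline utility. An article may leave the list of confounders to a fuller document.

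**Conclusion.** The point holds as a choice of analysis to improve before data are seen. Chance imbalance is the wrong test for a covariate, and the rule fixes the primary model only after unblinded data are available. The cost is forgone precision and avoidable flexibility.

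Its size rests on an assumed correlation. Against a post-only comparison, baseline adjustment adds about 4, 10 and 17 percentage points of power at r = 0.3, 0.5 and 0.7. Against a change-type contrast it adds about 18, 10 and 2 points, so at high correlation little is lost if T0 is an outcome. The article does not say how T0 is coded, so both comparisons are shown. The calculations treat one follow-up time with equal SDs and approximate the four-visit GEE; they are not its exact power.

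**What to change.** Replace the covariate sentence in the Statistical analysis section as follows.

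- Delete the imbalance criterion.
- State that the primary model adjusts for baseline ISI, either as a covariate on the T1 to T3 outcomes or with T0 kept as an outcome and the baseline means constrained equal. If T0 becomes a covariate, also state that the treatment effect is the group difference at the named visit. A time × group term over T1 to T3 alone would test only whether the effect changes after treatment.
- Include the stratification factors, sleep medication and PWP, and say how PWP enters, since the number of PWPs is not given.
- Name any further prognostic variables now.
- Take dropout predictors from a list named in advance. Use them in the GEE, in an imputation model on which the GEE itself is run, or in a sensitivity analysis.

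The cost is wording only. ISI and sleep medication are recorded at baseline and PWP is known at randomisation. The sample size is unchanged, and the article reports that recruitment has only just begun.

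### Cohen's d is defined as a post-test difference over the SD of change scores, so it is on neither the scale the protocol describes nor the scale of the planned 0.50

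*Protocol article*

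**What the plan says.** In the protocol article, Statistical analysis, the between-group test is a time-by-group interaction from GEE. The size of the effect is then described with Cohen's d, computed by "dividing the difference in scores of the two groups at post-test by the pooled standard deviation of change scores". The next sentence interprets it: "This can thus be interpreted as the number of standard deviations the intervention group scores better than the control group". Missing values are multiply imputed for this calculation.

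The Sample size section plans on a Cohen's d of 0.50 for the Insomnia Severity Index (ISI), introduced as a "conservative estimation of a post treatment effect size".

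The article gives no other definition of d. It gives no SD for the ISI and no correlation between baseline and post-test scores.

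**The concern.** A standardised difference is easy to read when numerator and denominator describe the same quantity. Here the numerator is "dividing the difference in scores of the two groups at post-test", which concerns scores at one time, and it is divided "by the pooled standard deviation of change scores", which concerns the spread of differences between two times. The SD of change depends on how strongly baseline and post-test scores correlate. The same separation between the arms at post-test therefore gives a different d according to that correlation, which has nothing to do with how far apart the arms are.

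Two statements in the article are affected. The interpretation sentence reads naturally as SDs of scores, but the formula gives SDs of change. The planned value of 0.50 is presented as a post-treatment effect size, so anyone who sets the reported d beside it will compare two scales under one name. Cohen's d is the standardised measure that the section names for the magnitude of effect, so that comparison is likely to be made.

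**Working it through.** **Inputs from the document.** Numerator, denominator and interpretation of d: Statistical analysis. Planned d of 0.50, power 80%, alpha 0.05, dropout 20%, and 80 per arm (160 in total): Sample size. Allocation 1:1: Randomization.

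**Inputs that must be assumed.** The correlation r (taken from 0.2 to 0.8) and the ratio k = SD_pre/SD_post (taken as 0.75, 1 and 1.25), both the same in the two arms. Alpha is taken as two-sided, which the article does not state.

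**Step 1: the plan's own figure.** A two-sample t-test with d = 0.50, two-sided alpha 0.05 and 80% power needs 63.8, so 64 per arm. Then 64/(1 − 0.20) = 80 per arm, 160 in total. This reproduces the stated size. (The normal approximation gives 63, and 63/0.8 rounds up to 79. A one-sided test gives 50, and 50/0.8 rounds up to 63, which does not reproduce.) The arithmetic would be the same whichever SD the 0.50 refers to. It is the section's description of 0.50 as a post-treatment effect size that places it on the post-test scale.

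**Step 2: what the formula returns.**

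SD_change = √(SD_pre² + SD_post² − 2·r·SD_pre·SD_post)

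Reported d = (post-test difference)/SD_change = (ordinary post-test d) × SD_post/SD_change = (ordinary post-test d)/√(1 + k² − 2rk)

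With equal SDs (k = 1) the divisor is √(2(1 − r)). For example, at r = 0.7 it is √0.6 = 0.775, and 0.50/0.775 = 0.645.

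**Step 3: reported d when the true post-test d is 0.50.**

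| r | k = 0.75 | k = 1 | k = 1.25 |
|---|---|---|---|
| 0.2 | 0.445 | 0.395 | 0.348 |
| 0.3 | 0.474 | 0.423 | 0.371 |
| 0.4 | 0.510 | 0.456 | 0.400 |
| 0.5 | 0.555 | 0.500 | 0.436 |
| 0.6 | 0.614 | 0.559 | 0.485 |
| 0.7 | 0.698 | 0.645 | 0.555 |
| 0.8 | 0.830 | 0.791 | 0.667 |

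**Step 4: where the formula happens to be right.** It returns the ordinary d only if SD_change = SD_post, that is k² = 2rk, so r = k/2. The crossover is r = 0.375 at k = 0.75, r = 0.5 at k = 1 and r = 0.625 at k = 1.25. Above it the reported d is too large, and below it too small.

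**Step 5: check on the remedy.** Post-test difference over post-test SD returns 0.50 for every r and k. Post-test difference over baseline SD returns 0.50/k. That is free of r, but it is 0.50/0.75 = 0.67 when k = 0.75, so it recovers the post-treatment scale only if the two SDs are equal.

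**The case against.** The strongest defence is that d is purely descriptive here. The test is the GEE interaction, and the improvement and recovery percentages, relative risk, number needed to treat and cost-effectiveness results do not use d. It can also be recomputed from the same data at any time. All of that stands, and it limits how serious the point is.

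A second defence is that, under randomisation, the expected post-test difference equals the expected difference in change. The formula then estimates an effect in SDs of change, which is a legitimate quantity. That is true in expectation, but the article neither labels it so nor interprets it so, and the quantity is still not a post-treatment d.

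Third, the size of the distortion rests wholly on assumed values of r and the SDs. This also stands. Even its direction for the ISI is unknown from the document.

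A reader might go further than the document allows:
- **That the formula always inflates the effect, or that the turning point is always r = 0.5.** Neither holds. The turning point is half the ratio of baseline to post-test SD.
- **That the result cannot be compared with any cited effect.** The article does not say how the earlier trial's 1.06 or the meta-analysis values of 0.80, 0.66 and 0.55 were standardised, so only the mismatch with the planned 0.50 can be shown.
- **That particular outcomes, such as alcohol use, would be inflated most, or that d would differ across outcomes only through r.** No correlations are given for any outcome, and true effects and SD ratios differ too.
- **That leaving chance baseline imbalance in the numerator is a separate error.** It is a feature of any unadjusted post-test d, and its expectation is zero under randomisation. It is a reason to prefer an adjusted difference, no more.

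**Conclusion.** The formula is wrong as written. It pairs a post-test difference with the SD of change, and nothing else in the article corrects it. The result is not, in SDs of scores, "the number of standard deviations the intervention group scores better than the control group", and it is not on the scale of the 0.50 used for planning.

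Under the assumed r of 0.2 to 0.8, a true post-test d of 0.50 would be reported as 0.395 to 0.791 with equal SDs, 0.445 to 0.830 with SD_pre/SD_post = 0.75, and 0.348 to 0.667 with a ratio of 1.25. These are illustrations of sensitivity, not predictions for this trial.

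A reader might infer that the trial's power or conclusions are at risk. They are not on this account: the p-values, type I error, power and the 160 patients do not depend on how d is reported. The point is a should-fix.

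**What to change.** Use a numerator and a denominator that match. The preferred version is the between-group difference at post-test, ideally the model-based, baseline-adjusted estimate, divided by the pooled SD of post-test scores. This agrees with the planned post-treatment d and makes the existing interpretation sentence correct once it says that the SD is that of post-test scores. A baseline SD would also remove the dependence on r, but it does not by itself restore the post-treatment scale (Step 5 of the working).

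If the SD of change is to be kept, divide the between-group difference in change by it, label the result as an effect size for change, reword the interpretation sentence, and do not set it beside the planned 0.50 without that label.

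The cost is one sentence in the Statistical analysis section. No data, patients or change to the test or sample size are needed. The choice should be fixed before the outcome data are analysed, so that the standardiser is not picked with the results in view.
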